### Pharmacological treatment(s)

Any concomitant medication used during the study will be recorded as well as any other required medication administered during hospitalization according to current guidelines and clinical practice. Any patients not taking long-term acetylsalicylic acid (ASA) before the procedure will receive a 300 mg oral dose of ASA at the time of inclusion in the study. All patients will continue their chronic treatment after the study termination as prescribed by their cardiologist. Dual antiplatelet therapy regime (DAPT) after discharge will be decided by the responsible physician according to current recommendations, bearing in mind the recommendations on DAPT switching if required [14, 15].

### Invasive multimodal physiology assessment

An intracoronary pressure and temperature sensor-tipped guidewire (St. Jude Medical) will be used to measure distal coronary pressure and the index of coronary flow derived from the coronary thermodilution method as previously described [11]. Three thermodilution curves will be obtained from a hand-held, 3 ml injection of room temperature saline, initially at baseline and then during maximal hyperemia, the latter achieved by an infusion of 140 µg/kg/min of adenosine via a large peripheral vein. Mean transit time (Tmn) at baseline and during maximal hyperemia will be derived from the thermodilution curves. Simultaneous recordings of mean aortic pressure (guiding catheter, Pa) and mean distal coronary pressure (distal pressure sensor, Pd) will be obtained at baseline and during maximal hyperemia. The coronary flow reserve (CFR) will be calculated from the ratio of hyperemic to baseline Tmn. The index of microcirculatory resistance (IMR) will be calculated using the following equation: $$ {\text{IMR}} = {\text{Pa}} \times {\text{Tmn }}\left[ {\left( {{\text{Pd}} - {\text{Pw}}} \right)/\left( {{\text{Pa}} - {\text{Pw}}} \right)} \right], $$where Pw is the coronary wedge pressure measured during vessel occlusion at the time of PCI. Calculation of IMR using Yong’s correction [16] (that does not require the incorporation of Pw) will be performed and reported. The FFR will be calculated from the ratio of distal to proximal pressures at maximal hyperemia.

## Sample size and statistical analysis

As no studies are currently available reporting on the impact of Ticagrelor on microvascular function compared to Clopidogrel, we based our sample size calculation on a previous study [10] showing that the intracoronary administration of Nicorandil after PCI resulted in a difference of 10 units in deltaIMR with respect to the control group. Assuming a difference of 10 in deltaIMR, in the experimental vs. control group, and a standard deviation of 10 a total of at least 20 patients per group would be needed to achieve an 80% power at a 2-sided alpha of 0.025, which accounts for the multiple primary endpoint design with a Bonferroni correction. Therefore, we aim to enroll 25 patients per group in order to take into account a 25% of potential missing data or major protocol violation due to clinical reasons (for example: clinical instability of patient between index and PCI procedure leading to urgent revascularization before completion of the protocol).

Any subject who took no trial medication will be eliminated from the full analysis set. Although a low or null proportion of exclusions due to treatment non-compliance is expected, any potential biases arising from this exclusion will be addressed. Imputation techniques will be used in an attempt to compensate for missing data. Regarding missing data, for primary endpoints, listwise deletion will be used meanwhile for the rest of analyses, listwise deletion or multiple imputation will be considered, depending on the type of missing process and on the quantification of the efficiency loss due to case deletion in each case. An investigation will be made concerning the sensitivity of the results of analysis to the method of imputation, especially if the number of missing values is substantial.

Being PREDICT a multicenter trial, the influence of the centre on the treatment effect and other endpoints will be addressed, and further adjustment will be done in the subsequent analysis, if necessary. Special attention will also be paid to the role of baseline measurements of the primary variable and diabetes treatment. Moreover, obese patients and those with previous myocardial infarction are subgroups of interest and their influence on the primary variables will be addressed and interpreted. However, subgroup analyses here have a exploratory nature, and therefore, interpreted cautiously.

A diagram of the participant flow showing for each group, the number of participants who were randomly assigned, received intended treatment, and were analyzed for the primary outcome will be provided, as recommended by the CONSORT 2010 statement.

Categorical variables will be reported as frequencies and percentages. Continuous variables will be expressed as mean ± SD or as median (Q_1_–Q_3_), according to the normality of their distribution, which will be tested with the Shapiro–Wilk test. Bartlett’s test will be performed to demonstrate homogeneity of variances between more than two groups. Primary endpoints will be assessed using the Student *t* test, if the samples are normally distributed or their variances are homogeneous; or Mann–Whitney U test, otherwise. P values will be corrected in order to account for the multiple endpoint. For the analysis of secondary variables, comparisons between continuous variables will be performed using the (paired or unpaired) Student *t* test or Mann–Whitney U test. The IMR at baseline, before PCI, and after PCI will be compared with an ANOVA for repeated measures or with the Friedman test, as appropriate. Comparisons between categorical variables will be evaluated using the Fisher exact test or the Pearson Chi square test, as appropriate. Correlations between continuous variables will be assessed using the Pearson or the Spearman rank correlation test. A 2-way ANOVA for repeated measures will be used to detect changes in IMR levels over time in the two study groups. Finally linear and logistic regression models will be carried out in order to identify predictors of periprocedural myonecrosis and delta-IMR. Analysis will be performed both in the full analysis set and a per protocol analysis and any differences between them would be the subject of explicit discussion and interpretation. In case of having multiple stenoses in some patient, additional adjusted analysis will be provided. Statistical analyses will be performed using the R statistical software [17] and p values <0.05 (2-tailed) will be considered significant. Whenever possible, estimates will be accompanied by confidence intervals.

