## Methods

### Trial design and objectives

The PRotective Effect on the coronary microcirculation of patients with DIabetes by Clopidogrel or Ticagrelor (PREDICT) trial (http://www.clinicaltrials.gov No. NCT02698618) is a prospective, multicenter, randomized, open-label study designed to investigate the protective effect of Ticagrelor over Clopidogrel on the coronary microcirculation during PCI in patients with T2DM or pre-T2DM. The primary endpoint aims to document (i) a decrease in coronary microcirculatory resistance caused by treatment onset (Ticagrelor > Clopidogrel; mechanistic effect) and (ii) a lower increase in microcirculatory resistance caused by PCI (Ticagrelor < Clopidogrel; protective effect). A detailed list of endpoints is reported in Table 1 and defined in the Additional file 1: Appendix. A dedicated eCRF platform will be designed and hosted in the http://www.cardiogroup.org website.

**Table 1 Tab1:** Study endpoints

Primary
Decrease in microcirculatory resistance caused by treatment onset (Ticagrelor > Clopidogrel)—*mechanistic effect*
Increase in microcirculatory resistance caused PCI (Ticagrelor < Clopidogrel)—*protective effect*
Secondary
Myocardial necrosis associated with PCI damage, assessed by cardiac biomarkers^a^
Absolute resistance value after PCI
Incidence of severe microcirculatory impairment defined as IMR > 29 after PCI
Subgroups analysis
Obese subjects

*PCI* percutaneous coronary intervention

^a^Third universal definition of myocardial infarction [40]

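### Single-step Bonferroni on the two primary endpoints gives away power that a Holm step-down would recover with the same patients and the same 5% family-wise error

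*Protocol article*

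**What the plan says.** All references are to the protocol article.

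- **Aim.** The section Trial design and objectives says: "The primary endpoint aims to document (i) a decrease in coronary microcirculatory resistance caused by treatment onset (Ticagrelor > Clopidogrel; mechanistic effect) and (ii". The quote stops at the second limb, which is a smaller rise in resistance caused by PCI on ticagrelor. Table 1 lists both effects as primary, and the abstract joins them in the same way.
- **Sample size.** The section Sample size and statistical analysis gives one calculation: "Assuming a difference of 10 in deltaIMR, in the experimental vs. control group, and a standard deviation of 10". From this it concludes that "a total of at least 20 patients per group would be needed to achieve an 80% power at a 2-sided alpha of 0.025".
- **Multiplicity.** The same sentence explains the 0.025 as a level "which accounts for the multiple primary endpoint design with a Bonferroni correction".
- **Enrolment.** To allow for losses, "we aim to enroll 25 patients per group".
- **Analysis.** Later in the same section the commitment is only that "P values will be corrected in order to account for the multiple endpoint". No method is named there. The general significance threshold is two-tailed 0.05.

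**The concern.** The plan wants to show two effects, and the only correction that it names is Bonferroni. In its single-step form each endpoint must reach two-sided 0.025 whatever happens on the other. Once one null hypothesis has been rejected, only one remains, and testing it at 0.05 would still keep the family-wise error at 5%. The stricter level then costs power and adds no protection.

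The loss falls on the outcome that the objectives describe, which is evidence for both effects. It is unlikely to be eased by correlation between the endpoints. The pre-PCI IMR enters both changes: baseline minus pre-PCI, which should be larger on ticagrelor, and post-PCI minus pre-PCI, which should be smaller. A chance error in that shared reading helps one comparison and hurts the other. With about 20 evaluable patients per group, there is little power to spare.

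**Working it through.** **Inputs.** From the sample-size section: difference 10, SD 10 (standardised effect 1), two-sided 0.025 per endpoint, 20 evaluable per group, 25 enrolled. Two assumptions are needed. The same effect and SD are applied to both endpoints, because the article gives one set only. The correlation between the endpoints, measured in the direction of benefit, is not given and is varied from -0.5 to +0.5.

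**Step 1: reproduce the plan's figure.** With the normal approximation,

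n per group = 2 × (z for 0.9875 + z for 0.80)² × (SD/difference)² = 2 × (2.2414 + 0.8416)² × 1 = 19.01, rounded up to 20.

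This is the printed number. At n = 20, the power of one test at 0.025 is 82.1% by the normal approximation and 79.3% by the exact noncentral t. At 0.05 the exact figure is 86.9%. The 80% is therefore correct as power for one endpoint.

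**Step 2: where the -0.5 comes from.** Let b, p and q be the baseline, pre-PCI and post-PCI readings, with common variance s² and common pairwise correlation r. The two benefits are b - p and p - q.

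- Cov(b - p, p - q) = s²(r - r - 1 + r) = -s²(1 - r)
- Each variance = 2s²(1 - r)
- Correlation = -0.5

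Equal variances and equal correlations are assumptions, so zero and +0.5 are shown as well.

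**Step 3: check by hand at zero correlation** (exact t powers 0.7926 at 0.025 and 0.869 at 0.05).

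- Both significant, Bonferroni: 0.7926² = 0.628
- Both significant, Holm: 2 × 0.7926 × 0.869 - 0.7926² = 1.3775 - 0.6282 = 0.749
- At least one significant, either rule: 1 - (1 - 0.7926)² = 0.957

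**Step 4: simulation across correlations.** Two-sample t tests, 20 per group, 100,000 trials per setting. Bonferroni requires both p < 0.025. Holm requires the smaller p < 0.025 and the larger p < 0.05. By symmetry, per-endpoint power under Holm is the average of P(at least one) and P(both under Holm).

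| Correlation | Both, Bonferroni | Both, Holm | Gain (points) | At least one, either rule | Per endpoint, Holm |
|---|---|---|---|---|---|
| -0.5 | 59.7% | 73.8% | 14.1 | 98.8% | (98.8 + 73.8)/2 = 86.3% |
| 0 | 62.8% | 75.0% | 12.2 | 95.8% | (95.8 + 75.0)/2 = 85.4% |
| +0.5 | 67.4% | 77.6% | 10.2 | 91.0% | (91.0 + 77.6)/2 = 84.3% |

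A separate run of 200,000 trials gave 59.9%, 62.8% and 67.5% for Bonferroni and 73.8%, 74.9% and 77.5% for Holm.

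**Step 5: error control.** With both nulls true, the two rules reject at least one hypothesis in exactly the same trials. The simulated family-wise error was 4.7% at correlation -0.5 and 4.9% at 0. With one null true, Holm tests it at 0.05 at most.

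**Step 6: other evaluable numbers** (correlation -0.5 to 0). A 25% loss from 25 leaves 18.75, about 19.

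| Evaluable per group | Both, Bonferroni | Both, Holm |
|---|---|---|
| 19 | 55.5-58.8% | 70.1-71.4% |
| 20 | 59.7-62.8% | 73.8-75.0% |
| 25 | 77.3-78.3% | 86.8-87.0% |

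**The case against.** A reader might infer that the printed 80% misstates the trial's chance of success, which would really be about 60%. The document does not support that. The 80% is tied to one difference, one SD and a level of 0.025, so it is visibly a per-endpoint figure, and it is correct as such. Nowhere is success made conditional on both endpoints. The word joining the two aims is not a decision rule, and splitting alpha is what one does when either endpoint may support a claim. On that reading the chance of success is about 91-99%, and Holm does not change it. The Rationale also ranks the hypotheses, calling protection during PCI primary and the reduction before PCI secondary, which further weakens a both-must-succeed reading.

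If both endpoints were required, no alpha split would be needed. Testing each at 0.05 would give joint power of 74.1%, 75.6% and 78.4% at correlations -0.5, 0 and +0.5. Holm comes within one point of this and remains valid for a claim on either endpoint alone, so it serves both readings.

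It is also true that Bonferroni is named only where the size is justified, and that the analysis text leaves the method open. Sizing at 0.025 and analysing by Holm would contradict nothing, and an analysis plan not shown here may already say so. What stands is that the only method this document names is the less powerful of two that control the same error.

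**Conclusion.** The point holds as one about efficiency. The sample size is right, the 80% is right per endpoint, and type I error is controlled. What is lost is power for the second endpoint. At 20 evaluable per group, the chance of showing both effects is about 60-68% under Bonferroni and 74-78% under Holm, a gain of about 10 to 14 points. Power for each endpoint rises from 79% to about 84-86%.

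These figures assume a difference of 10 and an SD of 10 on both endpoints, and a correlation between -0.5 and +0.5 that the document does not give. The levels also move with the number evaluable. The direction does not depend on any of this, because Holm rejects everything that Bonferroni rejects.

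**What to change.** In Sample size and statistical analysis:

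1. Replace the open commitment to correct p values with Holm for the two primary endpoints: test the smaller p value at two-sided 0.025 and, if it is significant, the other at two-sided 0.05. Equivalently, compare Holm-adjusted p values with 0.05. This works for the t test and for the Mann-Whitney test alike.
2. Keep the Bonferroni-based sample size, which is sufficient for each endpoint.
3. State that the 80% is power for each primary endpoint separately. If power for both is quoted as well, give it with its assumptions.

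The change is to wording only, with no more patients and no loss of error control. The small cost is that confidence intervals matching the Holm decisions are less simple to construct. The 97.5% intervals that go with Bonferroni can be reported alongside, with a note that the second Holm decision may be significant where that interval still includes zero.

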**Fig. 1 Fig1:**
[figure not shown]
Study flow chart. *CFR* coronary flow reserve, *IMR* Index of Microvascular Resistance, *FFR* Fractional Flow Reserve, *AMI* acute myocardial infarction, *PCI* percutaneous coronary intervention, *CK*-*MB* creatine kinase myoband, *cTn I* cardiac troponin I

Patient identification and enrollment: All consecutive patients with stable ischemic heart disease and T2DM or pre-T2DM referred for coronary angiography will be screened as potentially eligible for the study. Assessment of coronary stenosis severity using Fractional Flow Reserve (FFR) and the status of the microcirculation including measurement of coronary flow reserve (CFR) and Index of Microvascular Resistance (IMR) [10, 11] will be performed with the same pressure guidewire as part of the diagnostic process. Revascularization will be considered whenever a FFR ≤0.80 is found in a stenosis amenable to PCI. Eligible patients requiring PCI will be informed of the characteristics of the study and invited to participate.Randomization: Patients will be randomly assigned (1:1 ratio) to receive either Clopidogrel (600 mg loading dose followed by a daily dose of 75 mg) or Ticagrelor (180 mg loading dose followed by a dose of 90 mg b.i.d). The groups will be balanced according to the presence or absence of obesity [12] (Body Mass Index ≥ 30 kg/m^2^) [12] with the implementation of a dedicated randomization list. Patients who are already on oral treatment with Clopidogrel 75 mg/day are allowed to enter the protocol. According to randomization arm these patients will be assigned, after baseline assessment of microcirculation, to continue Clopidogrel 75 mg/day or be switched to Ticagrelor (180 mg loading dose followed by a dose of 90 mg b.i.d).PCI procedure: PCI procedure will be deferred for at least 48 h after the first administration of the study drug treatment in order to allow approximately 5 mean-half life times of their active metabolites, similar to a previously published study [9].3.1.Pre-PCI: Multimodal physiological evaluation (FFR, CFR, IMR) will be repeated.3.2.PCI: For all patients undergoing PCI, unfractioned heparin will be administered at the time of PCI. The PCI procedures will be performed using standard techniques using and second generation Drug Eluting Stents. Balloon pre-dilatation will be mandatory before stent implantation using a semi-compliant balloon with a diameter smaller than 75% of the distal reference vessel size in order to avoid confounding effects related to pre-dilation [13]. Post-dilation will be performed according to clinical practice although it will not be mandatory. All PCI characteristics (materials and techniques) will be recorded.3.3.Post-PCI: After stent implantation, multimodal intracoronary physiological evaluation will be repeated (FFR, CFR, IMR).

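### Enrolling 25 per group covers a 20% loss, not the stated 25%; at 25% loss about 18.75 per group remain, short of the plan's own minimum of 20

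*Protocol article*

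**What the plan says.** The section 'Sample size and statistical analysis' of the protocol article gives the whole derivation. The effect and spread are fixed first: "Assuming a difference of 10 in deltaIMR, in the experimental vs. control group, and a standard deviation of 10". The result follows: "a total of at least 20 patients per group would be needed to achieve an 80% power at a 2-sided alpha of 0.025", where the 0.025 is a Bonferroni share for two primary endpoints. The next sentence goes from required to enrolled patients: "we aim to enroll 25 patients per group in order to take into account a 25% of potential missing data or major protocol violation". Its example of such a loss is a patient who becomes unstable between the index and PCI procedures and is revascularized urgently before the protocol is complete.

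The same section settles three points that decide who reaches the primary test:

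- Missing primary-endpoint data are handled by listwise deletion.
- Patients who never took study drug leave the full analysis set.
- Results are reported for both the full analysis set and a per-protocol set.

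The primary comparison is a Student t test, with Mann–Whitney U as the alternative. No other part of the article gives a different loss rate or a larger enrolment.

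**The concern.** The sentence attaches 25% to the patients who are lost, so it should be a fraction of those enrolled. The enrolment figure instead comes from adding 25% to those required. The two operations differ: adding a fraction d to the required number protects against a loss of d/(1+d), which is 0.25/1.25 = 20% here.

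At stake is whether the stated power survives the stated loss. A reader of the article will take it that the trial can lose a quarter of its patients and still have 80% power for each primary endpoint. On the article's own numbers it cannot. The article prints the required number, the loss rate and the enrolment, so this is an inconsistency within the text and not a detail left to a fuller document.

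**Working it through.** **Inputs**, all from 'Sample size and statistical analysis' except the 1:1 allocation, which is in the randomization step of the study flow: difference δ = 10, SD σ = 10, two-sided α = 0.025 per endpoint, power 80%, required 20 per group, enrolled 25 per group, loss 25%, Student t test.

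**1. The plan's 20 reproduces.** By the normal approximation,

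n = 2 (z₀.₉₈₇₅ + z₀.₈₀)² (σ/δ)² = 2 (2.2414 + 0.8416)² × (10/10)² = 19.01, rounded up to 20.

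Rounding 19.01 up to 20 leaves some slack: normal-approximation power at 20 per group is 82.1%.

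**2. The inflation step.**

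- What was done: 20 × 1.25 = 25.
- What 25% loss leaves: 25 × (1 − 0.25) = 18.75 per group, or 37.5 in total.
- The loss that 25 per group does cover: 1 − 20/25 = 20%.
- What 25% loss would need: 20/(1 − 0.25) = 26.67, so 27 per group (54 in total, against 50).

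**3. Power at the numbers that remain.** Normal approximation: Φ(√(n/2) · δ/σ − 2.2414). t test: noncentral t with 2n − 2 degrees of freedom and noncentrality √(n/2) · δ/σ.

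| Evaluable per group | Normal approximation | Student t test |
|---|---|---|
| 18 | 77.6% | 74.1% |
| 18.75 (25% loss from 25) | 79.4% | 76.2% |
| 19 | 79.98% | 76.8% |
| 20 (20% loss from 25) | 82.1% | 79.3% |
| 20.25 (25% loss from 27) | 82.7% | 79.8% |
| 21 | 84.1% | 81.5% |
| 25 (no loss) | 90.2% | 88.5% |

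Example, normal approximation at 18.75: √9.375 = 3.062; 3.062 − 2.2414 = 0.820; Φ(0.820) = 0.794.

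**4. Separating two effects.** The t test needs 20.3 per group for 80%, so 20 gives 79.3%. That gap of 0.7 points is ordinary rounding between methods and has nothing to do with loss. The inflation slip takes 20 down to 18.75: 79.3 − 76.2 = 3.1 points by the t test, and 82.1 − 79.4 = 2.7 points by the normal approximation.

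**The case against.** The arithmetic is hard to dispute, so the case on the other side is about size and reach. Most of it stands.

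- **By the plan's own method the shortfall is trivial.** The approximation that yields 20 still gives 79.4% at 18.75 per group, about 0.6 points under target, because rounding up left slack. This stands, and it is why both columns are shown.
- **Not every lost patient leaves the primary test.** A reader might infer from listwise deletion that the whole 25% disappears. The documents do not say so. The allowance covers major violations as well as missing data, and a violator with measured IMR can stay in the full analysis set. The whole loss bears on that analysis only if all of it is missing IMR. In the per-protocol analysis it bears more directly. The article's own example, urgent revascularization before completion, would probably lose the measurement, so this narrows the point without removing it.
- **An allowance is not the realised loss.** A reader might infer that a null result would come from an underpowered trial. That does not follow: if loss is 20% or less, at least 20 per group remain. The article also promises a flow diagram with the numbers analysed, and confidence intervals where possible, so the precision achieved will be visible.
- **Other assumptions matter more.** The difference of 10 is borrowed from a nicorandil study. Taking SDs of 9 and 11 purely as illustrations, t-test power at 19 per group would be 85.6% and 67.8%. A 3-point change is small beside that.
- **The authors may have meant 25% more than 20.** Possibly, but the text labels 25% as the share missing or violating, so the wording would still need correcting.

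**Conclusion.** The point holds as a minor arithmetic error. Twenty required, 25 enrolled and 25% lost are incompatible; 25 per group covers 20% loss. At 25% loss about 18.75 per group remain, with power of about 79.4% (normal approximation) or 76.2% (t test), of which roughly 3 points are due to the slip.

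These figures assume δ = 10, SD = 10, two-sided α = 0.025 and equal loss in both groups. They also assume either that all of the loss is missing primary-endpoint data or that the analysis is per protocol. Where some violators have measured IMR, the effect in the full analysis set is smaller.

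Two stronger readings are not supported. The figure of 74.1% belongs to 18 in both groups, which is a 28% loss (7/25), more than the plan allows for. And the 79.3% at 20 per group is not a second error in the plan, only the usual difference between the normal approximation and the t test.

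**What to change.** Change one sentence in 'Sample size and statistical analysis', in one of two ways:

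1. State that 25 per group allows for 20% of patients being lost to missing data or major violations, since 25 × 0.80 = 20. This keeps the enrolment and the required number.
2. Keep the 25% and state its consequence: about 19 per group evaluable and about 76–77% power by the t test (76.2% at 18.75, 76.8% at 19).

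Neither adds a patient or changes the design. If the sponsor wants to keep both the 25% allowance and 20 evaluable, the enrolment is 27 per group, four more patients in total. Starting from the t-test requirement of 21 it would be 21/0.75 = 28 per group. The size of the slip does not by itself call for either increase.

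### The primary test leaves out pre-drug IMR and the obesity balancing factor; adding them to the treatment-onset comparison is a free gain in power, but the PCI comparison needs a different model

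*Protocol article*

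**What the plan says.** Table 1 and the section on trial design and objectives give two primary endpoints, both changes in IMR. The first is "Decrease in microcirculatory resistance caused by treatment onset (Ticagrelor > Clopidogrel"), from baseline to the repeat measurement before PCI. The second is ("ii) a lower increase in microcirculatory resistance caused by PCI (Ticagrelor < Clopidogrel; protective effect"), from before to after PCI.

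For both, the section on sample size and statistical analysis states: "Primary endpoints will be assessed using the Student" t test, with Mann–Whitney as the fallback. No covariate or stratum is named.

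Two pre-treatment variables are at hand. The flow-chart text has IMR measured at the diagnostic procedure, before study drug, and says of randomisation: "The groups will be balanced according to the presence or absence of obesity" (BMI of 30 kg/m² or more). In the statistical section, baseline gets this: "Special attention will also be paid to the role of baseline measurements of the primary variable and diabetes treatment". Obesity returns as a subgroup of interest with exploratory status. Regression models for delta-IMR are planned, but to find predictors.

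**The concern.** A change score subtracts the starting value but does not remove its influence. If the two readings have equal variance and correlation r below 1, patients who start high tend to fall and those who start low tend to rise, so the change stays negatively correlated with baseline. This has two consequences in a trial of about 20 evaluable patients per arm. Variance that baseline could explain stays in the standard error, and a chance imbalance in baseline IMR carries over into the treatment contrast.

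Obesity was judged important enough to balance on. If it predicts the IMR response, leaving it out makes the standard error somewhat too large. The attention promised to baseline is tied neither to the primary test nor to a model, so whether and how to adjust could be settled after the data are seen.

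**Working it through.** **Inputs from the article.** The statistical section gives a difference of 10 and SD of 10 ("Assuming a difference of 10 in deltaIMR, in the experimental vs. control group, and a standard deviation of 10") and the error rates ("80% power at a 2-sided alpha of 0.025, which accounts for the multiple primary endpoint design with a Bonferroni correction"). Allocation is 1:1.

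**Assumed, because the article does not give it.** The correlation r between successive IMR readings, taken as 0.3, 0.5, 0.7 and 0.9, with equal variances at each reading.

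**1. The plan's own figure.** n = 2 × (10/10)² × (z₀.₉₈₇₅ + z₀.₈₀)² = 19.01, rounded up to 20 per group. This agrees with the plan. With the noncentral t distribution, 20 per group gives 79% power (82% by the normal approximation), and 21 would be needed for 80%.

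**2. Variance gain for endpoint 1.** Let s² be the variance of one reading.
- Change score: 2s²(1 − r)
- ANCOVA on the starting value: s²(1 − r²)
- Ratio: (1 + r)/2

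Holding the SD of the change at 10, the adjusted SD is 10 × √((1 + r)/2). Power uses the noncentral t at 20 per group, charging 2 degrees of freedom for baseline and obesity and crediting obesity with no gain.

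| r | Variance ratio | Adjusted SD | Power at 20 per group |
|---|---|---|---|
| unadjusted | 1 | 10 | 79% |
| 0.3 | 0.65 | 8.06 | 94% |
| 0.5 | 0.75 | 8.66 | 90% |
| 0.7 | 0.85 | 9.22 | 86% |
| 0.9 | 0.95 | 9.75 | 81% |

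A simulation of 4000 trials gave 93%, 90% and 85% at r = 0.3, 0.5 and 0.7.

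**3. Chance imbalance for endpoint 1.** With s = 10/√(2(1 − r)), a baseline difference of two standard errors is 2s√(2/20). It shifts the change-score contrast by (1 − r) times that: 3.7, 3.2 and 2.4 units at r = 0.3, 0.5 and 0.7, against an assumed effect of 10. ANCOVA removes this shift.

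**4. Obesity alone.** If obesity explains an assumed 2% to 10% of the variance of the change, the normal-approximation sample size falls from 20 to 19 or 18 per group.

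**5. Endpoint 2, change kept as outcome, pre-drug IMR as covariate.** If all three readings are equally correlated, pre-drug IMR is uncorrelated with the pre-to-post-PCI change and saves 0% of variance. Under a first-order autoregressive pattern it saves r²(1 − r)/2: about 3%, 6% and 7% at r = 0.3, 0.5 and 0.7.

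**6. Endpoint 2, outcome replaced by post-PCI IMR adjusted for pre-drug IMR.** Suppose the drug lowers IMR by 10 at onset, the reduction persists, and there is no protection during PCI. Simulated at 20 per group and alpha 0.025, with r from 0.3 to 0.7, this model rejects in 84–93% of trials under equal correlation and in 65–91% under the autoregressive pattern. The planned t test on the change rejects in 2–3%, as it should.

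**The case against.** The strongest reply is that nothing here is wrong in the strict sense. The two-sample test is valid, the sample size matches it, and leaving out a balancing factor makes the test at worst slightly conservative. This stands, and a reader who infers an invalid analysis or a wrong sample size goes further than the article allows.

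A reader might also infer that baseline is ignored. It is not: the change score subtracts the starting value, and the text mentions both baseline and obesity. What is true is that neither is a covariate in the primary test.

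A third tempting inference is that one ANCOVA would bring the same gain to both endpoints. It would not. The ratio (1 + r)/2 requires the covariate to be the starting value of the change. For endpoint 2 that value is the pre-PCI IMR, taken at least 48 h after the first dose, so it is itself affected by treatment and conditioning on it changes the question. Step 6 shows what happens if the pre-drug IMR is used with a replaced outcome. This matters because the Discussion names protection during PCI as the trial's main purpose.

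On obesity, the article's premise is mainly a larger drug effect in obese or diabetic patients. That is effect modification, which a main-effect term does not capture. The likely gain from obesity is therefore small.

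Finally, it can be said that a condensed article leaves covariates to a fuller document. That would answer a complaint about missing detail. It does not answer this one, because the article states the primary test and the comment is on that choice.

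**Conclusion.** The point holds as a free improvement, mainly for endpoint 1. There, adjustment raises power at 20 per group from 79% to between 81% and 94% over assumed correlations of 0.9 down to 0.3, and protects against chance imbalance in baseline IMR. The size depends on a correlation the article does not give, on equal variances at the two readings, and on the plan's difference and SD of 10; the gain nearly vanishes as r approaches 1. For endpoint 2, pre-drug IMR saves only about 0% to 7% of variance under the structures examined, so no comparable gain can be claimed.

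**What to change.** **Endpoint 1.** Pre-specify as primary an ANCOVA of pre-PCI IMR on treatment, pre-drug baseline IMR and obesity stratum, on the log scale if IMR is skewed, with the rule for choosing the scale fixed in advance. Keep the unadjusted t test as supportive.

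**Endpoint 2.** Keep the pre-to-post-PCI change as the outcome and add the obesity stratum. Pre-drug IMR may be added; say in advance whether it is. Do not replace the outcome with post-PCI IMR adjusted for pre-drug IMR, and do not condition on the on-drug pre-PCI IMR.

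**Cost.** Two degrees of freedom and a change of wording. No new measurements or patients are needed, and the planned sample size can stay.
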